## Abstract

**Background::**

Numerous observational studies show associations between family meal frequency and markers of child cardiovascular health including healthful diet quality and lower weight status. Some studies also show the “quality” of family meals, including dietary quality of the food served and the interpersonal atmosphere during meals, is associated with markers of child cardiovascular health. Additionally, prior intervention research indicates that immediate feedback on health behaviors (e.g., ecological momentary intervention (EMI), video feedback) increases the likelihood of behavior change. However, limited studies have tested the combination of these components in a rigorous clinical trial. The main aim of this paper is to describe the *Family Matters* study design, data collection protocols, measures, intervention components, process evaluation, and analysis plan.

**Methods/design::**

The *Family Matters* intervention utilizes state-of-the-art intervention methods including EMI, video feedback, and home visiting by Community Health Workers (CHWs) to examine whether increasing the quantity (i.e., frequency) and quality of family meals (i.e., diet quality, interpersonal atmosphere) improves child cardiovascular health. *Family Matters* is an individual randomized controlled trial that tests combinations of the above factors across three study Arms: (1) EMI; (2) EMI+Virtual Home Visiting with CHW+Video Feedback; and (3) EMI+Hybrid Home Visiting with CHW+Video Feedback. The intervention will be carried out across 6 months with children ages 5-10 (n=525) with increased risk for cardiovascular disease (i.e., BMI ≥75%ile) from low income and racially/ethnically diverse households and their families. Data collection will occur at baseline, post-intervention, and 6 months post-intervention. Primary outcomes include child weight, diet quality, and neck circumference.

**Discussion::**

This study will be the first to our knowledge to use multiple innovative methods simultaneously including ecological momentary assessment, intervention, video feedback and home visiting with CHWs within the novel intervention context of family meals to evaluate which combination of intervention components are most effective in improving child cardiovascular health. The *Family Matters* intervention has high potential public health impact as it aims to change clinical practice by creating a new model of care for child cardiovascular health in primary care.

**Trial Registration::**

This trial is registered in clinicaltrials.gov (Trial ID: NCT02669797). Date recorded 5/02/22.

## Background

Cardiovascular disease (CVD) is a highly prevalent public health problem [1,2]. CVD is the leading cause of death for one in four adults in the US and affects over 30% of minoritized populations [1]. While CVD peaks in middle age, risk factors begin in childhood and may provide a critical window for intervening to mitigate risk [3]. Children ages 7-10 are at a key age when precursors of CVD begin to be observed, but before the manifestation of disease such as high blood pressure, body mass index (BMI), cholesterol [3,4] and less healthful dietary intake, fewer hours of physical activity, and more sedentary behaviors [5]. To date, there has been low to moderate success with lifestyle behavior interventions for children at risk for CVD and the persistent disparities across race/ethnicity calls for a new and innovative way to intervene [6]. Prior research has identified evidence-based intervention targets and strategies that when combined may provide an innovative approach for improving child cardiovascular health (CVH).

Prior interventions to increase child CVH have not been anchored around a specific family context/routine such as family meals. Instead, interventions often take a “kitchen sink approach” targeting multiple home environment factors (e.g., eating, physical activity, sedentary behavior, parenting) across multiple contexts (i.e., home, school, daycare). These interventions have had limited success [18]. Family meals are unique in that they create a nexus where multiple parenting and familial behaviors related to childhood obesity occur simultaneously (e.g., parent feeding practices, interpersonal behaviors, availability of healthy foods, portion size, modeling healthy eating) and can be intervened on–which rarely occurs in any other context. Furthermore, intervening on one specific context/routine (i.e., family meals) may also seem more doable to parents [19].

Second, some observational studies have shown the need to examine **family meal “quality”** (i.e., dietary intake, interpersonal atmosphere), in addition to family meal quantity, to better understand key protective factors of family meals [7,12,20]. Specifically, prior studies have shown associations between interpersonal interactions (e.g., non-controlling food parenting practices, positive communication/connection) during meals and better diet quality of foods served at family meals (e.g., fruits/vegetables, whole grains), lower child weight status, and higher child diet quality [20,21]. The few existing RCTs examining family meal frequency and child CVD risk found that solely increasing the frequency of family meals was not associated with lower weight status in children [17]. Thus, interventions targeting both family meal quality and quantity will have a higher likelihood of improving child CVH.

Additionally, studies have identified barriers to carrying out family meal routines such as busy schedules, parental stress, lack of food prep/cooking skills, and child behaviors (e.g., picky eating) [22,23]. Research by our team showed that parents experiencing high **stress** levels earlier in the day, were less likely to have family meals, served less healthy foods at mealtimes, and were more likely to engage in controlling feeding practices later the same day [24,25]. Interventions including family meal quantity and quality, as well as strategies to reduce barriers (e.g., stress) to carrying out family meals are needed.

Third, research shows that providing **immediate feedback on behavior** (i.e., ecological momentary intervention (EMI), video feedback) within a specific context (e.g., family meals) results in more behavior change over time [26], compared to solely utilizing parent education [18]. These findings suggest that teaching parents what to do is not enough, rather watching one’s own behavior(s) and receiving feedback that reinforces positive behaviors or prompts different behaviors is necessary. Meta-analyses show that **video feedback** in parenting interventions is feasible, has low participant burden, results in moderate to large effects on parenting behaviors, and results in sustainable behavior change [27].

**Ecological momentary intervention (EMI),** or mobile health (mHealth), uses smartphones to send text messages to participants to intervene on behaviors in real-time as they unfold, moment-by-moment, over time and across contexts [28]. For example, a participant responds to a text earlier in the day regarding their stress level and source(s) of stress (e.g., too many things to do) then, an EMI message is sent providing suggestions to support them in making a healthful choice for family meals in the face of stress (e.g., tip for making a quick pasta meal more healthful by adding a vegetable stir in) [29,30]. EMI studies from other fields have shown significant improvement in targeted behaviors (e.g., medication compliance, smoking cessation) [31,32], high feasibility [32], validity and reliability [33,34], few logistical problems [26], and low burden [35].

Fourth, interventions utilizing **community health workers** (CHWs) who can meet participants “where they are at,” both with regard to readiness for change and in their own environment (i.e., **home visiting**) are associated with better outcomes [36]. CHWs link care across clinic and home contexts and have high success with addressing obesity [36], diabetes [36] and other chronic conditions [36]. In addition, given the rise of **virtual technology** during the COVID-19 pandemic, the need to test virtual versus in-person measurement and delivery of home visiting interventions in a rigorous RCT is key to confirm the benefits of these approaches [37].

The **main aim** of the ***Family Matters Intervention*** is to target a well-documented family context associated with child CVH (i.e., family meals) using innovative real-time methods (i.e., EMI, video feedback) with CHWs in both virtual and in-person delivery modes to increase child CVH using a three-arm RCT (see Figure 1). The three Arms include: EMI (Arm 1); EMI+Virtual Home Visiting (HV) with CHW+Video Feedback (Arm 2); and EMI+Hybrid HV with CHW+Video Feedback (Arm 3). Our **overall hypothesis** is that increasing both the quantity and quality of family meals will improve child CVH. Our **main study hypotheses** include (see Figure 1):

Hypothesis 1: BMI percentile (%ile) and neck circumference will decrease and diet quality will increase in children in Arm 3 compared to children in Arms 1 or 2.Hypothesis 2: Family meal quantity and quality will increase, controlling food parenting practices (e.g., restriction) will decrease, and parent coping skills will increase in parents in Arm 3 compared to parents in Arms 1 or 2.Hypothesis 3: BMI %ile will decrease in siblings in Arm 3 compared to siblings in Arms 1 or 2.

### Theoretical Framework

Family Systems Theory (FST) [38] guides the current study. According to FST, the family environment is the most proximal influence on child CVH [39,40]. FST suggests that intervening on individual-level behavior (e.g., dietary intake) has limited success unless the family-level behavior sustaining or overriding the individual-level behavior (e.g., fruits/vegetables served at family meals, food parenting practices) changes too [39,41]. FST also suggests that healthful behaviors learned in one family context (e.g., family dinner meal) will generalize to other family contexts (e.g., breakfast, lunch, snacks) [41,42]. Thus, in the current study it is expected that positive parenting practices learned in the family meal context will generalize to other eating occasions and contribute to child CVH overall. Also, including multiple family members (e.g., parents, grandparents, siblings) in the intervention increases the likelihood of sustainable family-level change [7,20].

## Methods

This protocol has been written following the guidelines of the Standard Protocol Items Recommendations for Interventional Trials (SPIRIT) checklist (Additional file 1). A SPIRIT figure is also provided below to demonstrate the flow of the study (see Figure 2).

### Study Design

The *Family Matters* intervention is a single site RCT with child as the unit of randomization and analysis (see Figure 3). The study is funded by the National Institutes of Health (HL151978) and is registered at clinicaltrial.gov (Trial ID: NCT02669797; May 2, 2022). This RCT lasts 12 months for each family, with a four month active intervention phase, a two month maintenance phase, and data collection at baseline, 6 months (i.e., post-intervention), and 12 months (i.e., 6 months post-intervention). All study materials are created in both English and Spanish.

### Study Recruitment

Children (n=525) and their families are recruited via family medicine and pediatric primary care clinics in Minneapolis and St. Paul, MN. Recruitment is ongoing for 42 months. Eligible children receive a letter inviting participation. Parents then fill out a REDCap survey assessing eligibility criteria.

### Inclusion Criteria:

Children ages 5-10, their primary caregiver (e.g., parent, grandparent, aunt) and at least one sibling.Children at high risk for CVD, defined as BMI ≥75th percentile [43].Children from African American/Black, Asian, Hispanic, Native American, or White households who speak Spanish or English.Children who consume ≤3 family meals per week [12].

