#### “Try-it-Yourself” Activities.

Families are given food-related (e.g., recipes, meal planning strategies) and interpersonal (e.g., food prep with kids, family meal communication game, stress reduction) activities to try out in between visits to increase their self-efficacy in preparing family meals on their own and reinforce messages they are taught during HVs. The study child and all siblings in the home are also given an activity book with games that reinforce session content.

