## STATISTICAL ANALYSIS PLAN

### Overview.

This study is powered for three pairs of tests [72] to evaluate intervention effectiveness: (a) Arm 2 vs. 1, (b) Arm 3 vs. 1, and (c) Arm 2 vs. 3 over three time points. Multi-level, general linear mixed models (MLMM) with a clinic random intercept that nests participants within clinics to address any clinic differences in the recruitment populations, with participant random slopes for time to examine intervention treatment effects, and conditional fixed effects regression models (within-child analytic contrast against baseline), are the primary analytical models for all study hypotheses. Participants’ randomized condition will be examined irrespective of adherence to the study protocol in accordance with an intent-to-treat (ITT) analysis. After the intervention has been fully administered, data will be assessed for balance across arms, outliers, missingness, and other modeling assumptions. Although randomization is expected to produce balance on measured and unmeasured characteristics, variables will be considered for inclusion as controls in adjusted analyses to reduce test statistic variance [73]. We expect little missing data based on our prior work, but if needed, we will employ methods recommended for clinical trials to minimize analytical assumptions required when missing data are present (e.g., follow up all randomized participants prior to unblinding [74], evaluating if results from the primary analysis differ when sensitivity analyses are performed [75]). Reasons for participant withdrawal and non-adherence will be analyzed and reported in the final ITT analysis [76].

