**Sibling-Level Outcomes**	
**Sibling BMI%ile**	**Procedure:** Sibling height and weight are taken during the virtual visit using the same procedures as child height and weight. **Measure:** Sibling BMI%iles are calculated using the same procedures as child BMI%ile.

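### The models named for every hypothesis have no family level, so the sibling BMI percentile analysis would understate its standard errors whenever a family contributes more than one sibling

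*Protocol article*

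**What the plan says.** The Inclusion Criteria admit a child, the primary caregiver "and at least one sibling". This is a minimum, and no maximum is given. Under Study Arms and Randomization, families are allocated to the arms, and where several children qualify as the study child, one is drawn at random. No corresponding rule is given for siblings.

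Hypothesis 3 in the Background reads: "BMI %ile will decrease in siblings in Arm 3 compared to siblings in Arms 1 or 2". Table 1, under Sibling-Level Outcomes, says: "Sibling height and weight are taken during the virtual visit using the same procedures as child height and weight". It does not say how many siblings are measured or analysed. The section on Try-it-Yourself activities adds: "The study child and all siblings in the home are also given an activity book".

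The Overview of the Statistical Analysis Plan describes a linear mixed model "with a clinic random intercept that nests participants within clinics", "with participant random slopes for time to examine intervention treatment effects", together with conditional fixed effects models that contrast each child with its own baseline. These "are the primary analytical models for all study hypotheses". No family or household level is named. Aim 2 carries the detectable effect of 0.38 SD over from Aim 1 to sibling BMI percentile.

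**The concern.** Siblings in one household share the arm, the home visits, the parents and the meals. The article's theoretical framework treats the family as the nearest influence on a child's cardiovascular health, so correlated change among siblings is what the trial itself would expect. A clinic intercept does not absorb correlation within a household. The within-child contrast removes stable differences between families, but not a tendency of siblings to change together.

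If several siblings per family enter the model as separate participants, they are treated as independent given clinic. The interval for the arm difference in sibling BMI percentile is then too narrow, and an effect on siblings is declared too often. This matters because Hypothesis 3 is one of the three main study hypotheses, although its outcome is secondary.

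**Working it through.** **Inputs from the article.** 175 per arm; two-sided critical value z = 2.77; 80% power; BMI percentile variance 18.8, so SD = √18.8 = 4.336; 0.38 SD stated for siblings under Aim 2.

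**Inputs not in the article, hence assumed.** Number of siblings analysed per family, m = 1, 2 or 3; correlation of change between siblings of one family, ρ = 0.1 to 0.5.

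**Step 1: the plan's own figure.** For two arms of n independent children, d = (2.77 + 0.842) × √(2/n). With n = 175, d = 3.612 × 0.1069 = 0.386, or 0.386 × 4.336 = 1.67 points. This agrees with the stated 0.38 SD and 1.67. The figure therefore corresponds to one independent child per family. (With 15% loss, n = 148.75 and d = 0.419. The ICC value is blank in the text available, and a variance factor of about 0.85 would close that gap, so the figure is not called wrong here.)

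**Step 2: effect of ignoring the family.** Design effect DE = 1 + (m − 1)ρ. Ratio of reported to true standard error = 1/√DE. True two-sided error = 2 × [1 − Φ(z/√DE)].

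Worked case, m = 2 and ρ = 0.5: DE = 1.5; 1/√1.5 = 0.816; 1.96/1.225 = 1.600; true error 0.110.

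| m | ρ | DE | Reported/true SE | True error at nominal 0.05 | True error at z = 2.77 (nominal 0.0056) |
|---|---|---|---|---|---|
| 1 | any | 1.0 | 1.000 | 0.050 | 0.0056 |
| 2 | 0.1 | 1.1 | 0.953 | 0.062 | 0.008 |
| 2 | 0.3 | 1.3 | 0.877 | 0.086 | 0.015 |
| 2 | 0.5 | 1.5 | 0.816 | 0.110 | 0.024 |
| 3 | 0.1 | 1.2 | 0.913 | 0.074 | 0.012 |
| 3 | 0.3 | 1.6 | 0.791 | 0.121 | 0.029 |
| 3 | 0.5 | 2.0 | 0.707 | 0.166 | 0.050 |

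**Step 3: unequal family sizes.** If 50%, 35% and 15% of families contribute one, two and three siblings (assumed), the mean of m is 1.65 and the mean of m² is 3.25. DE = 1 + (3.25/1.65 − 1)ρ = 1.10, 1.29 and 1.48 at ρ = 0.1, 0.3 and 0.5. True error at nominal 0.05 is 0.061, 0.085 and 0.108, close to the case of two siblings in every family.

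**Step 4: simulation.** Change scores were simulated with no arm effect, 148 families per arm and 6,000 runs per setting. Ignoring the family gave error rates of 0.058, 0.085 and 0.109 for m = 2, and 0.075, 0.126 and 0.165 for m = 3, at ρ = 0.1, 0.3 and 0.5. With m = 1 the rates were 0.049 to 0.054. Analysing family means brought all settings back to 0.045 to 0.054.

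**Step 5: information once the family is modelled.** Effective number per arm = 175m/DE. For m = 2 this is 350/1.1 = 318, 350/1.3 = 269 and 350/1.5 = 233, in each case above 175.

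**The case against.** The strongest reply is that the article never says that more than one sibling per family is analysed. The eligibility wording is only a minimum, Table 1 gives a procedure without a count, and the plural in Hypothesis 3 proves little, since Hypothesis 1 also speaks of children in the plural although each household has one study child. The reference to all siblings in the home concerns activity books, not measurement. This stands, and it makes the point conditional. A reader might infer that the sibling standard errors are certain to be too small; the documents do not support that.

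Secondly, *participant* could mean the randomized unit, of which there is one per family. If sibling records were grouped under that unit, the participant term would act in part as a family term. This is a possible reading, but the article does not state it, and Study Design names the child as what is randomized and analysed.

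Thirdly, the correlation that matters is that of change, which is not given, and z = 2.77 was derived for nine tests of primary outcomes. Both are true. The sizes above are therefore a range under assumptions, and the last column only illustrates a stricter threshold.

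Two further inferences are tempting and fail. One is that the 0.38 SD for siblings rests on an inflated count of independent units. Steps 1 and 5 show that it matches one independent child per family, and that extra siblings with a family term would not worsen it. The other is that the random draw of the study child was a safeguard against clustering that was forgotten for siblings. The reason the article gives for it is bias from parental choice.

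Finally, an article condenses a fuller plan, and a rule for selecting siblings may well be there. That excuses the missing rule. It does not remove the difficulty that a model structure is stated and declared to apply to every hypothesis.

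**Conclusion.** The point holds in conditional form. The models declared for all hypotheses have clinic and participant levels and no named family level, while eligibility allows several siblings and all of them share one arm. If a family contributes more than one sibling to the Hypothesis 3 analysis, and each sibling is a participant in the model, the standard errors are too small.

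For two siblings per family and a correlation of change of 0.1 to 0.5, the reported standard error is about 5 to 18% too small, and the true error at nominal 0.05 is about 0.06 to 0.11. Three siblings in every family would give 0.07 to 0.17. Both the sibling count and the correlation are assumptions. With one sibling per family there is no error at all. The primary outcomes use one child per household and are unaffected.

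**What to change.** State whether one sibling or all measured siblings per family enter the Hypothesis 3 analysis.

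- **If all:** add a family random effect to the sibling BMI percentile model, or use standard errors clustered on family. Because correlated change is what matters, a family intercept alone may not suffice: include a family slope for time if it can be fitted, or rely on family clustering. In the conditional fixed effects model, where stable family differences already cancel, use family-clustered standard errors.
- **If one:** draw that sibling at random within the household and say so. No family term is then needed, but measurements on the other siblings go unused.

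The change amounts to one model term or one sentence, made before unblinded analysis. Its cost is slightly wider intervals for one secondary outcome. A family term or family clustering does no harm if each family turns out to contribute only one sibling. The 0.38 SD statement needs no change on this account.

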### Exclusion Criteria:

Children with medically necessary dietary restrictions (e.g., feeding tubes) or who are developmentally unable to participate (e.g., non-verbal).Non-custodial parent who lives with the child <50% of the time.Children participating in a weight management study.

### Study Arms and Randomization

Families are randomized into one of three intervention Arms: (1) EMI; (2) EMI+Virtual HV with a CHW+Video Feedback; and (3) EMI+Hybrid HV with a CHW+Video Feedback. All Arms receive 16 weeks (4 months) of EMI stress reduction and family meal tip messages via smartphones. Arms 2 and 3 additionally receive eight home visits by CHWs focused on family meal quantity and quality, a meal preparation activity, and video feedback on their family meal behaviors/patterns every-other-week for 16 weeks. Arm 2 receives all of these components virtually and Arm 3 receives these components half in person and half virtual (hybrid). In between weeks, families in Arms 2 and 3 complete a Try-it-Yourself activity to apply the new skills/behaviors they have been taught. All Arms receive an 8-week (2 months) maintenance phase allowing for progressively less support so they can increase self-efficacy and sustainability of behavior change.

Once participants complete their baseline data collection visit, they are randomized into one of three study Arms (n=175 per Arm). If households have multiple eligible children, one child is randomly selected to minimize bias that could affect generalizability due to parent selection. Randomization is stratified by five racial/ethnic groups (African American, Hispanic, Native American, Asian American, White; n≈105 per race group). Block randomization schedules were produced in PASS 2021 (Kaysville, Utah) to account for the racial/ethnic stratification. Schedules are maintained by the biostatistician to keep team members blinded.

